**OA patients:**
Knee and/or hip OA according to ACR criteria [58]
Kellgren & Lawrence grade 2–4 for hip/knee OA [42]
CRP < 10 mg/L within 3 months prior to enrollment [59]
**Sarcopenia patients:**
Sarcopenia without arthritis or other joint diseases according to the EWGSOPII criteria [56] of low muscle strength defined as HGS < 27 kg and <16 kg for males and females respectively (dynapenia). This group will primarily involve participants with probable sarcopenia (dynapenia) but may also encompass participants with confirmed sarcopenia (appendicular muscle Lean Mass (ALM)/height2 < 7.0 kg/m^2^ for males and <5.5 kg/m^2^ for females) as this is not a selection criterion. Severe sarcopenia will be excluded (gait speed <0,8 m/s)
**Exclusion criteria**
BMI < 18 or >35 kg/m²
Contraindications for exercise based on the physical activity readiness questionnaire (PAR-Q) or history of severe heart conditions (e.g., heart failure, MI < 3 months, other cardiac diseases)
Use of beta-blockers during intervention
Neurological, cachectic, inflammatory diseases or co-morbidities affecting muscle quality (e.g., MS, ongoing cancer treatment, radiotherapy/chemotherapy in last 6 months, hyperthyroidism, diabetes type 1/2, long COVID)
Participation in regular high-load training (>2x/week) within 2 months before enrollment
Recent ligament/muscle tears or injuries (<6 months)
Use of performance-enhancing drugs or supplements affecting muscle mass (e.g., protein powder)
Inability to schedule exercise therapy
Insufficient Dutch language skills or no informed consent

ACR American College of Rheumatology, CRP C-reactive protein, DMARD Disease Modifying Anti-Rheumatic Drug, EULAR European League Against Rheumatism, MS multiple sclerosis, OA Osteoarthritis, PARQ Physical Activity Readiness Questionnaire, RA Rheumatoid arthritis, SARC Sarcopenia.

### Procedures overview

Fig 2 provides an overview of the trial logistics. RA patients will be recruited from the Department of Rheumatology at both Reade and Amsterdam University Medical Center (location AMC). Newly referred OA patients to the Department of Rehabilitation at Reade will be invited to participate. Additionally, OA patients from an existing OA cohort at Reade, who have previously consented to be contacted for future research, will be informed about the study via email. These include patients who received treatment at Reade between 2020 and 2023. SARC patients will be recruited from the Department of Rehabilitation Medicine at the Amsterdam University Medical Centre. Patients with RA, OA, or SARC, who are deemed eligible for participation by their medical doctor (rehabilitation physician or rheumatologist) and meet the study criteria will be informed about the study by their specialist. Interested patients will receive an information letter and an IC form from their physician. Subsequently, the investigator will contact these patients by phone after one week to provide a verbal explanation of the study and to review and confirm the inclusion and exclusion criteria. If the patient expresses interest and appears to meet the criteria, an appointment will be scheduled for a screening visit with the investigator. After signing the IC form, the individual will be considered a study participant. During the screening visit, participants will perform a handgrip strength test or walk test, as both tests are indicative of general muscle strength. These tests will be used to exclude participants who are either too strong or too weak to participate (see Table 1 for inclusion criteria). Participants with moderate muscle weakness are included to ensure adequate training tolerance and to allow detection of exercise-induced improvements in muscle strength (primary outcome: peak torque). Final eligibility will be assessed by the primary investigator in consultation with a clinical team, including a rehabilitation physician and/or rheumatologist. Participant recruitment is expected to commence in January 2026 and is anticipated to conclude in August 2027. The total study duration, including follow-up and data analysis, is expected to extend beyond this period.

**Fig 2 pone.0356181.g002:**
[figure not shown]
Overview trial logistics: Participants with RA, OA, or SARC are recruited and screened for eligibility. After informed consent (IC), they are randomized (minimization) to the endurance or strength exercise group. Baseline assessments (T0, week 0) include biopsy, performance tests, blood, questionnaires, imaging, and isokinetic muscle strength measures. The exercise program starts within a maximum of 2 weeks after baseline assessment. After an 8-week supervised intervention, follow-up assessments (T2, week 9) repeat all baseline measures except the biopsy.

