### Randomization, blinding and allocation concealment

We will use minimization to ensure that the groups are maximally balanced with respect to the most important stratification factors, i.e., disease (RA, OA, SARC) and gender [32]. Randomization will be performed using a centralized, computer-generated minimization procedure via an open-source online tool (OXMAR; [33]). The personnel responsible for participant enrollment will not have access to the random allocation sequence. Outcome assessors and data analysts will be blinded to treatment allocation. Participants and physiotherapists will not be blinded due to the nature of the intervention.

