### Outcome measures

Fig 1 lists all descriptive data, primary and secondary outcomes, and other measures (e.g., treatment adherence and process measures).

The primary outcome is isokinetic muscle strength (*peak torque)* assessed using an isokinetic dynamometer Biodex System (Enknee Enraf-Nonius, the Netherlands)). **Peak torque** will be measured in both upper legs using knee extension test. Participants will first perform a familiarization trial. Subsequently, they will complete three maximal-effort repetitions at an angular velocity of 60°/s to assess the isokinetic strength of the quadriceps for each leg. The average torque (in Newton-meters, Nm) produced by the quadriceps per leg will be calculated and normalized to body weight (Nm/kg). For analysis, values from the index knee (i.e., the most affected knee) will be used [36]. In addition to absolute peak torque (Nm), relative muscle force will be assessed by calculating torque relative to physiological cross-sectional area (PCSA) as derived from 3D ultrasound (Nm/cm^2^). This provides an indication of muscle quality (i.e., force-generating capacity per unit muscle area).

Measurements will be performed at the start and end of the exercise intervention (except the muscle biopsy, which will be only taken prior to the intervention).

Secondary outcome measures include muscle endurance, and i) muscle morphology, (ii) mitochondrial function, and (iii) systemic inflammation (see Table 4). These parameters will be assessed using the Six minute Walk test (6MWT), an isokinetic dynamometer, 3D ultrasound (3D US), high-resolution respirometry (HRR), and blood-based biomarker analysis (Multiplex/ELISA), respectively and will be described in detail.

**Table 4 pone.0356181.t004:** Overview of secondary outcome measures, examples of measurements, related pathways relevant to the C4M study and the techniques to be applied.

Secondary Outcome Measure	Examples of read-outs	Related Pathway relevant to C4M	Technique to be applied
(i) **Muscle morphology**	• muscle belly length (ℓm); muscle fascicle length (ℓfasc); physiological cross-sectional area (PCSA); tendon length (ℓt); and muscle-tendon complex length (ℓm + t)	Muscle plasticity	3DUS
(ii) **Muscle mitochondrial function**	• Basal respiration; Leak respiration; NADH-linked respiration, Succinate-linked respiration, Maximal Oxidative Capacity; Maximum uncoupled respiration	Energy production (/ oxidative capacity)	high-resolution respirometry

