
Other measures: To enable in-depth characterization of the study participants the following variables will be collected.

a. Patient characteristics: Sociodemographic and lifestyle characteristics will be assessed using a standardized questionnaire, including age, gender, height, weight, educational level, employment status, marital status, smoking and alcohol use (including duration), symptoms, and use of walking devices. Comorbidity will be assessed using the Cumulative Illness Rating Scale (CIRS) [40], administered through a semi-structured interview. Information on current medication use will be obtained from the participant’s medical record. Protein intake will be assessed using a 24-h dietary recall conducted by a trained researcher. Protein intake (g/day) will be calculated using the Netherlands Nutrition Centre database.b. Anthropometrics: Body composition will be assessed using direct-segmental multi-frequency bio-electrical impedance analysis (DSM-BIA) (Biospace Co, Korea). DSM-BIA has been validated for assessing segmental and whole-body composition against dual energy X-ray absorptiometry (DXA) [41]. Muscle mass is expressed as SMM (kg), SMM index (SMI, kg/m^2^) by dividing SMM (kg) by height squared (m^2^) [30], relative SMM (%) by dividing SMM (kg) by body weight (kg)*100, ALM/height^2^ (kg/m^2^) by dividing ALM (kg) by height squared (m^2^) and fat free mass (%).c. Disease characteristics: diagnosis will be obtained from the participant’s medical record; Radiologic severity of osteoarthritis will be assessed using Kellgren and Lawrence grade (K&L) [42].d. Performance: handgrip strength will be assessed with a JAMAR**®** Dynometer (Patterson Medical, UK) [43,44]. Participants will be seated with elbows flexed at 90 degrees, shoulders adducted and forearms in a neutral position without support. They will be instructed to squeeze the dynamometer maximally three times per hand, alternating between the right and left sides. The highest recorded value (kg) will be reported; Short Physical Performance Battery (SPPB test) [45]. The SPPB assesses lower extremity function through three components i) Balance Test: Participants perform progressively challenging standing positions (feet together, semi-tandem, and full tandem stance) for up to 10 seconds each. ii) Gait Speed Test: Walking speed is measured over a 4-meter course. iii) Chair Stand Test: Participants complete five timed chair rises without using their arms for support. The time to complete the five repetitions will be recorded in seconds. The total SPPB score (0–12) reflects overall lower limb function, with higher scores indicating better performance.e. Patient-Reported Outcome Measures (PROMs) will be measured with online questionnaires: Numeric Rating scale pain (0–10) [46], PROMIS® short forms regarding fatigue (8a) version 1.0, physical function (8b) version 2.0, ability to participate in social roles and activities (8a) version 2.0 [47]. FitMáx© survey [48] is a questionnaire consisting of three single answer questions, about the maximum capacity of walking (scale from 0–13), climbing stairs (scale 0–10) and cycling (scale 0–11). By adding the participant’s sex, age and BMI, the FitMáx© model estimates the maximum oxygen uptake, expressed in ml/kg/min [48,49].

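### As written, unblinded participants are randomised before the T0 assessments, so baseline torque and questionnaires may be affected by knowing the arm, and some randomised patients may have no strength value

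*Protocol article*

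**What the plan says.** The order of events comes from the Fig 2 caption in the Protocol article. After recruitment and screening it states: "After informed consent (IC), they are randomized (minimization) to the endurance or strength exercise group. Baseline assessments (T0, week 0) include biopsy". The second of these sentences reads in full: "Baseline assessments (T0, week 0) include biopsy, performance tests, blood, questionnaires, imaging, and isokinetic muscle strength measures". The one after that is: "The exercise program starts within a maximum of 2 weeks after baseline assessment".

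The section on randomization, blinding and allocation concealment says that minimisation uses disease and gender. On blinding it says "Participants and physiotherapists will not be blinded due to the nature of the intervention" and "Outcome assessors and data analysts will be blinded to treatment allocation". It gives no time point for randomisation relative to T0, and none for telling the participant the result.

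Under Outcome measures, the primary outcome is peak torque on a dynamometer: "they will complete three maximal-effort repetitions at an angular velocity of 60°/s". On self-report, the same section says "Patient-Reported Outcome Measures (PROMs) will be measured with online questionnaires".

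In the Data analysis plan, the primary comparison is the time × exercise group term of a linear mixed model. The secondary models use the change in strength from T0 as the dependent variable. The analysis is to follow intention to treat, with multiple imputation of missing values.

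**The concern.** A baseline is safe to subtract or adjust for when it cannot have been influenced by the allocation. In the order given here, an unblinded patient may already know the arm when making the maximal effort that defines baseline torque, doing the performance tests, or answering the pain, fatigue and function questionnaires. Blinded assessors remove assessor bias, but they do not control how hard a patient pushes or what a patient reports.

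Two things are at stake:

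- **Bias.** Baseline torque is half of the primary contrast and part of every change score in strength. The trial's declared product is effect estimates and variability for planning later trials, so a biased contrast would be carried forward.
- **Missing data.** T0 includes a needle biopsy through a small incision. A patient who leaves after randomisation but before T0 counts under intention to treat, yet has no torque at either time point.

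**Working it through.** **Step 1: the order, section by section.**

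| Place | What it gives |
|---|---|
| Study design | Mentions randomisation first, then assessments at baseline and after 8 weeks; narrative order only |
| Procedures overview | Consent is signed, then screening tests; final eligibility is decided by the investigator with the clinical team |
| Fig 2 caption | Screening, consent, randomisation, T0, training within 2 weeks of T0, follow-up |
| Randomization section | Minimisation factors and blinding; no time point |

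No section puts T0 before randomisation, and none says the allocation is withheld until T0 is done.

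**Step 2: which T0 measures could shift.** Torque and the performance tests depend on effort, and the questionnaires are self-report. Respirometry on biopsy tissue, ultrasound dimensions and serum cytokines depend on neither. For those the concern is missing data, not a shift.

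**Step 3: how a shift enters the primary contrast.** Let D be the true difference in change, strength minus endurance. Let the endurance baseline be shifted by s, with follow-up unaffected. Then

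(strength change) − (endurance follow-up − [endurance baseline + s]) = D + s.

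The pass-through is one-for-one; a shift in the strength arm gives D − s. With complete pairs, the time × group term of the mixed model equals this difference in mean change. On one simulated data set both were −0.1003. Disease type and gender do not change over time, so they drop out of the within-patient change.

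**Step 4: illustration of scale.** The document gives no SD, no pre-post correlation and no expected shift, so all three are assumptions: SD 1, correlation 0.7 or 0.9, and an endurance baseline lowered by b SD. There are 30 patients per arm (the analysed number in the sample size section), no true effect, a two-sided 0.05 test and 10,000 simulated trials per setting. Bias is shown as an absolute value.

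| b (SD) | Bias in difference in change (SD) | False-positive rate, correlation 0.7 | False-positive rate, correlation 0.9 |
|---|---|---|---|
| 0 | 0.00 | 0.048 | 0.049 |
| 0.1 | 0.10 | 0.08 | 0.14 |
| 0.2 | 0.20 | 0.16 | 0.39 |
| 0.3 | 0.30 | 0.31 | 0.72 |

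Adjusting for the affected baseline does not rescue the estimate. The remaining bias is correlation × b, so at b = 0.2 it is 0.7 × 0.2 = 0.14 SD or 0.9 × 0.2 = 0.18 SD, as the simulation also gave.

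**Step 5: losses before T0.** Each one is 1/69 = 1.4% of the enrolled sample. The plan allows for 69 − 60 = 9 losses in all. A patient lost after T0 still has a baseline torque to inform the model and the imputation. A patient lost before T0 has none, so both torque values would have to be imputed from little more than screening and demographic data.

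**Step 6: is early allocation needed?** Minimisation uses only disease and gender, both known at screening, and a gap of up to 2 weeks between T0 and training already exists. Nothing in the document requires allocation before T0.

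**The case against.** The strongest reply is that the order is inferred. The only explicit time link is that randomisation follows consent; the sentence on T0 lists its contents without saying that it comes next. The figure itself is not shown, nor is the Fig 1 schedule. The caption is also loose elsewhere: it labels follow-up T2, while the analysis section uses T1. Even so, the caption otherwise runs in time order and no other text contradicts the natural reading.

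The second reply is that being randomised before T0 is not the same as being told before T0. This stands. A reader might infer that the protocol has patients learn their arm before baseline, but no disclosure time is given. If disclosure follows T0, the risk to torque and questionnaires largely disappears. Losses between randomisation and T0 would remain possible.

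Third, both arms are active, use the same exercises at the same target exertion, and have the same visit schedule. There is no untreated arm to disappoint patients, and no clear reason why effort would differ in one direction. This limits what can be said about size and sign. It does not show that the shift is zero.

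Two further readings go too far:

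- **Consent to the biopsy depends on the arm.** Informed consent precedes randomisation and no separate biopsy consent is described. What could depend on the arm is attending or declining the biopsy, or withdrawing.
- **Every predictor in the secondary models is compromised.** Most of them come from tissue, imaging or serum and are not open to effort or self-report.

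**Conclusion.** The point holds as a defect in the written sequence: the plan permits baselines taken with knowledge of the arm for an effort-dependent primary outcome, and it permits randomised patients with no strength value. The algebra of the pass-through is certain. The amount passed through is not known. The 0.1 to 0.3 SD shifts are assumptions chosen to show scale, and the false-positive rates in particular are illustrative because the trial emphasises estimation over testing. Nothing in the document shows that a shift or an early loss will occur.

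The conclusion rests on reading the caption as chronological and on there being no statement about disclosure. Given that, and the exploratory aim, this is something the protocol should correct; it does not invalidate the design. It is worth correcting because a baseline affected by knowledge of the arm cannot be repaired in the analysis.

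**What to change.** State in Fig 2 and in the randomization section that minimisation is run only after eligibility is final and all T0 assessments, including the biopsy, are complete. Training slots can then be arranged in the existing window of up to 2 weeks.

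If allocation must stay before T0, state at minimum that participants are not told their arm until T0 is complete. That protects torque, performance tests and questionnaires, but not against losses between randomisation and T0.

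If practice already follows the recommended order, only the caption needs correcting.

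The cost is a few words and slightly later assignment to the supervised groups of at most four, which may need some scheduling care. No sample size or analysis model changes. Recruitment was expected to begin in January 2026, so the change should be made promptly.

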### Randomization, blinding and allocation concealment

We will use minimization to ensure that the groups are maximally balanced with respect to the most important stratification factors, i.e., disease (RA, OA, SARC) and gender [32]. Randomization will be performed using a centralized, computer-generated minimization procedure via an open-source online tool (OXMAR; [33]). The personnel responsible for participant enrollment will not have access to the random allocation sequence. Outcome assessors and data analysts will be blinded to treatment allocation. Participants and physiotherapists will not be blinded due to the nature of the intervention.

### Physiotherapists and training

Six physiotherapists from Reade, all experienced in treating patients with rheumatic diseases, will be trained to deliver the standardized exercise program. Prior to the start of the trial, the physiotherapists will complete a mandatory, comprehensive two-hour training session. The training includes an explanation of the intervention protocol and study procedures, followed by a one-hour practical session to familiarize the physiotherapists with the use of the training equipment and performing an adequate 10 repetition maximum (10 RM) test. Interim training sessions will be held during the trial to control and optimize the quality of the interventions.

### Intervention

The intervention consists of an 8-week exercise program. Participants will be randomized into the endurance or strength exercise group. Each week, participants complete three exercise sessions: two supervised by PTs in groups of max. four participants and one performed independently at home. Each session includes 6–8 full-body exercises from a predetermined list: three quadriceps-focused exercises, one hip or glute exercise, and two upper body exercises as appropriate (see S1 File). Exercises are performed using the Reforter™ (HapticLink, The Netherlands), fitness equipment (e.g., leg press), and resistance bands. The Reforter™ is an electronic pulley cable system that allows for: 1) concentric and eccentric muscle loading; 2) force adjustment based on position, speed, or reaction force; 3) instantaneous measurements of force [N], speed [m/s], position [m], power [W], and work [J]. The software allows for various settings and programs specific to endurance and strength focused training and provides feedback during the exercises. Physiotherapists use this data to tailor and adjust training loads.

After familiarization with the correct execution of exercises (week 1, initial three sessions), a 10-repetition maximum (RM) test will be performed for the exercises conducted on regular fitness equipment. The 10RM results are used to calculate the estimated 1RM using the Brzycki formula [34]. This process will be repeated in week 5, after which training intensity will be adjusted, and again in week 8.

Supervised sessions include a 5–10 min warm-up and a 5 min cool-down, with total session duration ranging from 45 to 60 minutes. All participants will perform the same exercises at an intensity of a of 7–8 on a 10-point physical exertion scale (see Additional file 1 supervised exercise).

The endurance group performs the exercises with a load of 30–45% of their 1RM, while the strength group performs the exercises with a load of 60–75% of their 1RM. For further details on sets, repetitions, and rest time, see Table 2.

**Table 2 pone.0356181.t002:** Exercise intervention of the supervised and home-based training for both endurance and strength group.

	Frequency	Intensity	Time
**Strength group**	2x/week at Reade/ supervised	10 repetitions 3 sets 90s rest between sets 60-75% 1RM	45-60mins (incl. warm-up & cool down); Progressive
	1x/week home-based/unsupervised	10 repetitions 3 sets	30 mins
**Endurance group**	2x/week at Reade/ supervised	20 repetitions 3 sets 60s rest between sets 30-45% 1RM	45-60mins (incl. warm-up & cool down); Progressive
	1x/week home-based/unsupervised	20 repetitions 3 sets	30 mins

RM: repetition maximum.

To ensure comparable workload between both groups, total training volume is calculated as [35]:

$$\begin{array}{c} Total\;training\;volume\;=\;sets*repetitions*load \end{array}$$

(see Table 3 for sample calculation). During each session, clinical parameters are monitored, and exercises will be adapted as needed.

**Table 3 pone.0356181.t003:** Sample workloads and total volume for endurance and strength exercises for each session, assuming 1RM = 100 kg. Total volume = sets*repetitions*load.

	Sets	Repetitions	Load	Volume	Total Volume (kg)

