**Strength**					
Weeks 1–2	3	10	60% 1RM	3 sets * 10 reps * 60 kg	1800
Weeks 3–4	3	10	65% 1RM	3 sets * 10 reps * 65 kg	1950
Weeks 5–6	3	10	70% 1RM	3 sets * 10 reps * 70 kg	2100
Weeks 7–8	3	10	75% 1RM	3 sets * 10 reps * 75 kg	2250

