**Endurance**					
Weeks 1–2	3	20	30% 1RM	3 sets * 20 reps * 30 kg	1800
Weeks 3–4	3	20	35% 1RM	3 sets * 20 reps * 35 kg	2100
Weeks 5–6	3	20	40% 1RM	3 sets * 20 reps * 40 kg	2400
Weeks 7–8	3	20	45% 1RM	3 sets * 20 reps * 45 kg	2700

RM: repetition maximum.

To guarantee safety, tolerability will be assessed in each session using a numerical rating scale for pain (NRS, scale 0–10) or, where appropriate, physical examination. For NRS > 5, training load is modified. PTs may provide tailored instructions during sessions, following the same procedure for both groups.

The home-based exercises are initially taught at Reade and consist of bodyweight and resistance bands exercises. Exercise selection is the same across groups. However, the strength group uses bands with greater resistance. Additionally, repetition counts and rest intervals mirror those used in supervised sessions. Patients are instructed to target an intensity of 7–8 on a 10-point physical exertion scale. To ensure adherence to the intended intensity level, patients are asked to be aware of effort using easily measurable physiological indicators such as breathing rate, perspiration, and muscle soreness. Exercises are regularly evaluated and adjusted as needed by the treating physiotherapist.

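### The protocol says training volume is calculated so that workload is comparable between arms, but its own schedule matches prescribed supervised volume only in weeks 1–2 and gives the endurance arm 20% more by weeks 7–8

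*Protocol article*

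**What the plan says.** The Intervention section sets the loads: "The endurance group performs the exercises with a load of 30–45% of their 1RM, while the strength group performs the exercises with a load of". The sentence ends with the strength arm's range, which is 60–75%. Table 2 adds three sets in both arms, with 10 repetitions and 90 s rest in the strength arm and 20 repetitions and 60 s rest in the endurance arm.

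The volume formula is then introduced with its purpose, "To ensure comparable workload between both groups, total training volume is calculated as" sets × repetitions × load, and the reader is sent to Table 3. The caption of Table 3 reads "Sample workloads and total volume for endurance and strength exercises for each session, assuming 1RM = 100 kg. Total volume = sets*repetitions*load". Its strength rows start at "3 sets * 10 reps * 60 kg" and end at "3 sets * 10 reps * 75 kg". Its endurance rows end at "3 sets * 20 reps * 45 kg".

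The primary analysis (Data analysis plan, item 1) estimates the effect of exercise type on isokinetic strength through the time × exercise group interaction.

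**The concern.** Comparable workload is presented as a property of the design, and volume is the quantity chosen to secure it. A reader will take it that the arms differ in how hard each repetition is loaded while total work is held roughly level. The Background points the same way, because it names the best loading strategy in these diseases as the open question.

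If the schedule itself makes volume diverge, that reading is not available. A result favouring endurance exercise, or a null, could partly reflect the extra volume in that arm. A result favouring strength exercise would have arisen despite less volume. The trial is meant to supply effect-size estimates for later confirmatory studies, so a team that relied on the workload statement would misunderstand what had been contrasted. The gap is widest in weeks 7–8, just before the week 9 follow-up assessment.

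**Working it through.** **Inputs.** Sets, repetitions and %1RM come from the Intervention text and Tables 2 and 3. The reference 1RM is 100 kg in both arms (Table 3 caption). The formula is the protocol's own: volume = sets × repetitions × load.

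**Step 1. Reproduce Table 3, per exercise and session.**

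| Weeks | Strength (kg) | Endurance (kg) | Difference (kg) | Endurance/strength |
|---|---|---|---|---|
| 1–2 | 3 × 10 × 60 = 1800 | 3 × 20 × 30 = 1800 | 0 | 1.000 |
| 3–4 | 3 × 10 × 65 = 1950 | 3 × 20 × 35 = 2100 | 150 | 1.077 |
| 5–6 | 3 × 10 × 70 = 2100 | 3 × 20 × 40 = 2400 | 300 | 1.143 |
| 7–8 | 3 × 10 × 75 = 2250 | 3 × 20 × 45 = 2700 | 450 | 1.200 |

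All eight printed volumes reproduce exactly, so the table contains no arithmetic slip.

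**Step 2. Sum over blocks.** Strength: 1800 + 1950 + 2100 + 2250 = 8100 kg. Endurance: 1800 + 2100 + 2400 + 2700 = 9000 kg. Ratio: 9000/8100 = 1.111. With two supervised sessions a week there are four sessions per block, giving 32,400 v 36,000 kg per exercise and the same ratio.

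**Step 3. Why the gap opens.** With equal sets and a common 1RM, the ratio is (20 × endurance %1RM)/(10 × strength %1RM) = 2 × endurance %1RM / strength %1RM. It equals 1 only when the endurance percentage is half the strength percentage. That holds at 30/60 but not at 35/65, 40/70 or 45/75. Each 5-point step adds 3 × 20 × 5 = 300 kg in the endurance arm and 3 × 10 × 5 = 150 kg in the strength arm, so the gap grows by 150 kg per block. The 1RM cancels, so the ratios do not depend on the 100 kg example. The same percentage ranges stand in the running text and in Table 2, so the pattern is not confined to Table 3.

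**Step 4. Sensitivity of the summed figure.**

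- *Week 1.* The 10RM test follows the three familiarization sessions of week 1. Leaving week 1 out gives (900 + 2100 + 2400 + 2700)/(900 + 1950 + 2100 + 2250) = 8100/7200 = 1.125.
- *Home sessions.* One session in three is at home, with bodyweight and bands and no stated %1RM. Suppose home volume were the same in both arms and equal to the strength arm's supervised volume per session. The ratio would be (2 × 9000 + 8100)/(2 × 8100 + 8100) = 26,100/24,300 = 1.074. If home sessions followed the supervised ratio, it would stay at 1.111. Both are assumptions. The protocol gives the strength arm stronger bands and fewer repetitions, so the true home ratio is unknown.

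**The case against.** **Comparable does not mean equal.** The text sets no tolerance, and Table 3 prints the divergence openly. Whether 11% over the supervised programme is still comparable is a matter of judgement. This stands in part. The 20% gap in the last block is harder to defend: it is built into the progression, always runs in the same direction and is not acknowledged in the text.

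**Table 3 is only a sample.** It shows one exercise at one 1RM, and 10RM testing is described only for regular fitness equipment. Delivered loads will also move with the week 5 retest, the pain rule and physiotherapist tailoring. This stands as a limit on scope: the figures describe prescribed supervised work, not delivered work or the whole programme. It does not remove the inconsistency, because the percentages are those prescribed in the text and Table 2, and no described step brings the two arms' volumes back together. Retesting would close the weeks 7–8 gap only if the strength arm's 1RM had become 2700/2250 = 1.20 times that of the endurance arm.

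**Both arms share the same exercises and an exertion target of 7–8 out of 10.** True, but this matches perceived effort. The sentence at issue uses volume as its measure of workload.

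**The primary contrast is between exercise types, not loads.** This stands. A reader might infer that unequal volume confounds or biases the primary estimate. The documents do not support that. Volume is part of the randomised package, together with load, repetitions and rest, so the time × group term estimates the package difference without bias from this source. Nor does the protocol say that a difference will be assigned to load alone. Even equal volumes would not isolate load, since repetitions and rest would still differ.

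**Conclusion.** The statement of purpose and the schedule do not agree. Under the protocol's formula, prescribed supervised volume per exercise is equal in weeks 1–2. For any common 1RM it is then higher in the endurance arm by 7.7%, 14.3% and 20.0%, and by 11.1% summed over blocks. The size rests on the percentages, sets and repetitions being delivered as tabulated, and on similar 1RM in the two arms.

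What changes is interpretation. The primary estimate is a valid comparison of two packages, and no stated model, sample size or decision rule depends on equal volume. It cannot be presented as the effect of load at comparable workload, whichever way the result falls.

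Two further readings go too far. The 11% is not the excess for the whole programme, because home-session load is not quantified. It is also not a forecast of what participants will actually do.

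**What to change.** 1. Reconcile the workload statement in the Intervention section with Tables 2 and 3. The clinical team must decide which stands; this review takes no position on the training prescription.
2. If the schedule stands, remove the comparable-workload claim. State that the arms differ by design in load, repetitions, rest and volume, and that the primary contrast is a package effect.
3. In either case, report delivered supervised volume by arm as a descriptive table, as far as the records allow. Logbooks are said to hold sessions attended and training intensity, and the Reforter measures force and work. However, the protocol gives tailoring of loads as the use of the device data and does not say that they are stored for analysis. Check this early. Home volume cannot be computed from what is described.
4. Do not adjust the primary model for delivered volume. It arises after randomisation and is part of what the arms were assigned to do.

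The cost is a change of wording, one descriptive table and a less favourable description of the contrast. The primary model and the sample size do not change.
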